### Compliance With Ethical Standards

MAAESTRO has been approved by the Ethics Committee northwest/central Switzerland (EKNZ2017-01552). All study procedures are in accordance with the provisions of ICH GCP and the 1964 Declaration of Helsinki and its later amendments. Written informed consent is obtained from each patient before enrolment. MAAESTRO is registered on ClinicalTrials.gov (NCT03344146) and on the Swiss National Clinical Trials Portal (SNCTP000002410).

### Safety and Data Monitoring Body

No safety issues are expected. Any serious study-related events, along with the events captured as secondary study outcomes will be reported to the ethics committee. There will be no independent steering or safety committee. An external study monitor will routinely perform on-site visits to ensure per-protocol study conduct.

## Discussion

MAAESTRO is designed with pragmatic eligibility criteria to ensure participants are as representative as possible of stroke survivors self-administering their medication. Our study uses MCCAs and includes polymedicated patients, for whom pillbox use is meaningful, as they comprise the vast majority of stroke patients in clinical practice (3).

To obtain objective adherence data in a real-life setting, we use electronic monitoring during a long observational phase without further interventions that might modify medication-taking behavior (4). This will allow us to search for non-adherence predictors, with emphasis on cognitive and neuroimaging characteristics, and for reliable self-report measures of adherence that best discriminate adherers from non-adherers. These will provide healthcare professionals with simple, inexpensive ways to identify patients at risk for non-adherence.

For the adherence-improving intervention we hypothesize that reminders will have the largest effect (14). We therefore designed and powered MAAESTRO to provide randomized evidence for their use. We expect that counseling and MCCAs will have an additional adherence-improving effect, which we will assess in before-after comparisons. Furthermore, we will capture patient-reported device usability and satisfaction to complement the intervention's evaluation.

MAAESTRO is not powered to determine the impact of non-adherence on clinical outcomes. However, the detailed electronic intake records will allow close examination of possible deviations preceding clinical outcomes on an individual basis, which may provide insights into the mechanisms of stroke and bleeding occurrence in DOAC-treated patients.

In summary, MAAESTRO will provide comprehensive data on electronically monitored adherence and most importantly, randomized evidence for an adherence-improving intervention in the yet unexplored population of DOAC-treated patients with a recent stroke. Patient enrolment began in January 2018.

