### Randomization

Patients will be openly randomized to one of two groups in a 1:1 ratio at visit 1 in a crossover design: During the 6-month interventional phase, Group 1 will receive intake reminders for the first 3 months and Group 2 for the last 3 months. Randomization will be performed by a central computer through the web-based electronic case report form and include a variance minimization algorithm to ensure balancing for sex, age, NIHSS, and prior pillbox use.

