### Intervention

Key methodological instrument for MAAESTRO is the novel *Time4Med* medication system (Adherence Innovations, Hong Kong, China) which includes (i) the *Smart Card*, a small electronic device featuring a button that records intake date and time when pressed, (ii) the *Reminder Card*, a small electronic device that provides audiovisual intake reminders, and (iii) a MCCA with discrete medication storage compartments for each time of the day and day of the week, upon which the Reminder Card can be attached. Patients will record their intakes using Smart Cards throughout the 12-month-long study. After the 6-month observational phase, patients will receive pharmaceutical counseling during a medication review, the Polymedication-Check (13), and feedback on their intake history (Visit 1). Based on these, the optimal intake timepoints will be identified for each patient. Patients will receive MCCAs for use throughout the 6-month interventional phase along with attachable Reminder Cards, which will be programmed to provide reminders at the optimal timepoints for either the first or the last 3 months.

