### Study Outcomes

The primary outcome is non-optimal timing adherence to DOACs, defined as ≥ 1 dose omitted or taken outside of 25% of the prescribed dosing schedule (± 6 h for once-daily and ± 3 h for twice-daily DOACs). It will be calculated for the observational phase and for the two interventional-phase periods separately. Physician-initiated temporary treatment interruptions will not be considered non-adherence.

Secondary outcomes are:

non-optimal taking adherence (i.e., ≥ 1 dose omitted)timing adherence (i.e., proportion of doses taken within 25% of the prescribed dosing schedule)taking adherence (i.e., proportion of prescribed doses taken)self-reported adherence (based on the “Adherence self-report” and “A-14 scale” questionnaires, Table 1)clinical events including recurrent ischemic stroke, other ischemic events, bleeding and deathpatient-reported device usability and satisfaction

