### Statistical Analyses

The primary analysis will evaluate the reminders' effect on the primary outcome with a mixed-effects logistic model with Reminder Card (yes/no) as fixed and patient as random effect. Ancillary analyses will include the addition to the model of the following covariates:

the interventional-phase period (first/second), in order to assess for period effects (adherence differences between the two periods independent of the reminders' effect). We designed the study with a crossover design, assuming that adherence will be generally stable over the relatively short study duration and thus no period effects are expected.the interaction term “Reminder Card ^*^ period”, in order to assess for modification of the reminders' effect by the interventional-phase period (e.g., through a “carry-over effect”). We expect any interaction to be negligible.the type of DOAC (once-/twice-daily), in order to assess for association between adherence and type of DOAC.the interaction term “Reminder Card ^*^ type of DOAC”, in order to assess for modification of the reminders' effect by the type of DOAC.

Secondary analyses include the comparison of adherence outcomes between (i) the two interventional-phase periods and (ii) observational and interventional phase, as in the primary analysis. Non-adherence predictors (e.g., clinical and neuroimaging variables, mRS, MoCA test scores) will be assessed using logistic mixed lasso models. Descriptive statistics will be used for the comparison of self-reported with electronically recorded adherence, the association between adherence and clinical events and to present the rest of the data.

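### The before-after comparison assigned to counseling and pillboxes is not said to separate reminder from no-reminder months, so part of the reminder effect could be read as theirs

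*Protocol article*

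**What the plan says.** The Discussion of the protocol article gives the before-after analysis a specific purpose: "We expect that counseling and MCCAs will have an additional adherence-improving effect, which we will assess in before-after comparisons". Just before that, it says that reminders are expected to have the largest effect.

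Statistical Analyses lists the comparison as "ii) observational and interventional phase, as in the primary analysis". The model to which this refers back is described in these words: "mixed-effects logistic model with Reminder Card (yes/no) as fixed and patient as random effect".

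The content of the interventional phase is fixed elsewhere:

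- Randomization sets the order of reminders: "Group 1 will receive intake reminders for the first 3 months and Group 2 for the last 3 months".
- Intervention gives the pillbox to everyone for the whole phase: "Patients will receive MCCAs for use throughout the 6-month interventional phase along with attachable Reminder Cards". Each card is active in only one half of it.
- Study Outcomes counts a patient as non-optimal once a single dose in the window is missed or falls too far from schedule. On the windows themselves it says: "It will be calculated for the observational phase and for the two interventional-phase periods separately".

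**The concern.** The purpose is the effect of counseling and the pillbox. The named contrast is phase against phase. The pillbox is in use for all six interventional months, but reminders run for three of those six in every patient. A comparison of whole phases therefore measures counseling, pillbox and a share of the reminder effect together, and the unwanted share comes from the component the authors expect to be largest.

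No sentence restricts the comparison to months without reminders or says that the reminder effect is adjusted for. If neither is done, reminders alone could produce a favorable before-after result, and the stated purpose would invite reading it as a benefit of counseling and pillboxes.

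**Working it through.** **Inputs.** From Sample Size Estimates: 45% non-optimal timing adherence without reminders, a 20% effect of reminders, power 0.90, two-sided alpha 0.05, 12% drop-out, N = 130. From Randomization and Intervention: three months with and three without reminders per patient. The article does not say whether 20% is absolute or relative, so both readings are carried. It gives no between-patient variance, so random-intercept SDs are assumed.

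**1. Which reading reproduces N.** The plan used simulation; a two-proportion formula serves as a check.

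- Absolute (45% to 25%): (0.45 × 0.55 + 0.25 × 0.75) × (1.960 + 1.282)² / 0.20² = 0.435 × 10.51 / 0.04 = 114.3, so 115. With drop-out, 115 / 0.88 = 130.7, so 131 against the stated 130.
- Relative (45% to 0.8 × 45% = 36%): the same formula gives 620, or 705 with drop-out.

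A simulated mixed-effects logistic model with 130 × 0.88 = 114 completers (300 runs, SD 0 to 2) gives power 0.90 to 0.99 on the absolute reading and 0.28 to 0.42 on the relative one. The absolute reading is the one that fits.

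**2. Phase as the only fixed effect, true counseling and pillbox effect zero, windows of equal length.**

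| Reading of 20% | Observational | Without reminders | With reminders | Interventional average | Spurious benefit |
|---|---|---|---|---|---|
| Absolute | 45% | 45% | 25% | (45 + 25)/2 = 35% | 10 points |
| Relative | 45% | 45% | 36% | (45 + 36)/2 = 40.5% | 4.5 points |

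**3. The same setting in the mixed model** (114 patients, three windows each, 200 runs, SD 1 and 2).

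| Model | Reading of 20% | Phase log odds ratio (median) | True null rejected |
|---|---|---|---|
| Phase only | Absolute | −0.50 to −0.62 | 49% to 59% |
| Phase only | Relative | −0.21 to −0.28 | 12% to 18% |
| Phase + Reminder Card | Both | about 0 | 4.5% to 5.5% |

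**4. Why the added term is enough.** Reminders occur only in the interventional phase, so phase and Reminder Card define three conditions, not four. On the log-odds scale these are a (observational), a + b (interventional without reminders) and a + b + c (interventional with reminders). The wanted effect is b, the second condition against the first. A phase-only model estimates a mixture of b and b + c.

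**5. Window length.** The outcome counts any single missed or mistimed dose in a window, so it rises with the length of the window. Take 45% as a 3-month rate (an assumption). With constant, independent risk, the same behavior gives 1 − 0.55² = 69.8% over six months. If risk varies between patients (gamma with shape k, 6-month rate 1 − (1 + 2L/k)^−k, where L gives 45% over three months), it is 62.1% for k = 1 and 57.8% for k = 0.5. A 6-month observational window against 3-month periods would thus favor the intervention by about 13 to 25 points with no change in behavior. Isolating the no-reminder months does not correct this.

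**The case against.** The strongest reply is that pooling is nowhere stated. Study Outcomes calculates the outcome for each interventional period separately, so the data unit already distinguishes reminder from no-reminder time. Statistical Analyses runs the phase comparison in the manner of the primary analysis, whose model contains Reminder Card, and the ancillary analyses work by adding terms to that model. On this reading phase is added beside Reminder Card, which is the same mean structure as the three-level condition proposed here. The Discussion speaks of an additional effect and of comparisons in the plural, which also fits an effect over and above reminders. Finally, this is a condensed article, and the exact terms of a secondary model may sit in a fuller document.

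Much of this stands. A reader might infer that the plan does pool the months, that its contrast cannot answer the question, or that reminder benefit will be reported as benefit of counseling. The documents support none of these as fact, because the adjusted model is an available reading and is free of this bias.

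Three things remain:

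- The comparison is named as phase against phase, and the plainer reading is that phase takes the place of Reminder Card as the compared factor. Where the article adds terms beside Reminder Card, it lists them, and phase is not on that list.
- Calculating the outcome per period does not by itself separate the effects. Two period records under one phase factor still average over reminders.
- The article states both the contrast and the use to be made of it, and as named the first does not deliver the second. That goes beyond detail left to another document.

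**Conclusion.** The concern holds as a failure to separate the two effects, not as a demonstrated misattribution. If phase is the only fixed effect, the comparison would show a 10-point benefit (45% against 35%) with no counseling or pillbox effect at all, half the assumed reminder effect. It would be 4.5 points on the relative reading, which does not reproduce N. If the Reminder Card term is kept, this bias disappears.

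The size rests on the planning rates, on equal windows, and on no carry-over into months without reminders. The rejection rates also rest on assumed random-intercept SDs of 1 and 2. A reader might extend the point to the main result, but the randomized reminder comparison and its sample size do not depend on the before-after contrast.

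**What to change.** - **Contrast.** State that the counseling and pillbox effect is read only from interventional months without reminders against the observational phase. Fit a three-level condition in the mixed model: observational, interventional without reminders, interventional with reminders. Phase plus Reminder Card is equivalent.
- **Window.** Calculate the observational outcome for this contrast over three months, for example months 4 to 6, to match the interventional periods.
- **Sensitivity analysis.** Repeat the contrast in Group 2's first interventional period (months 7 to 9), the only reminder-free time after Visit 1 with no earlier reminder exposure. Group 1's reminder-free months follow its reminder months, so any carry-over would remain in them.

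**Cost.** Wording in the analysis plan only; the data are already to be collected. The contrast draws on three rather than six interventional months per patient, so it is less precise. The sensitivity analysis uses about half the patients (1:1 allocation). The contrast remains a non-randomized before-after comparison and should be reported as one.
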